### Postoperative data collection

Daily visits with study patients on all wards will be performed by clinical investigators and study nurses attached to the clinical study centre in order to collect information on the primary and secondary outcome parameters and to identify any AEs or SAEs. All surgeons will have to describe the closure technique that they performed on the pancreas on a standardised form that will be sent to them by email on the day of the index operation to record whether patients were treated according to the study protocol and were assigned to their groups truly at random. After discharge, all medical documents will be reviewed for assessment of the endpoints.

The DISPACT trial demonstrated an increased rate of POPF (30% to 36%) between day 7 and day 30 because this is when re-admission due to the need for further treatment occurred. To ensure the accurate assessment of our endpoints, DISCOVER patients will be called by phone at least 40 days after the operation to record postoperative development.

All patients will be invited to be seen at the outpatient clinic (European Pancreas Centre, Department of General, Visceral and Transplantation Surgery, Heidelberg) three months after their operation for regular follow-up consisting of oral and physical examination and blood tests. CT or MR imaging will be performed for regular follow-up, independent from this trial. The results will be used for postoperative data collection. Our flowchart summarises the data collection process with regard to timing and data type (Table 3).

**Table 3 T3:** Flowchart of the DISCOVER trial –course of examinations

**Visit**	**1**	**2**	**3**	**4**	**5**	**6**
	**Screening visit**	**Day of index OP**	**Daily postoperative ward visits**	**Day of discharge**	**Day 40 post OP (by phone)**	**3 months post-OP (optional)**
Past and current medical history	X					
Informed consent	X					
Physical examination and personal data (e.g., height, weight, age)	X					
Intraoperative randomisation (additional coverage yes/no)		X				
Basic study-related examination (to access endpoints)		X	X	X	X	X
Quality of life (EQ-5D questionnaire)	X			X	X	
AE, SAE		X	X	X	X	X
Drainage parameters (enzyme levels)			X	X		
Survival		X	X	X	X	X

### Primary and secondary endpoints

#### Primary endpoint

The primary endpoint of this trial is the rate of occurrence of POPF, as defined by the International Study Group on Pancreatic Fistula (ISGPF) [4]. A POPF is defined as the abdominal secretion of any measureable volume with amylase content greater than three times the upper normal value of serum amylase according to the centre-specific lab standards. Grading of a POPF mainly depends on its impact on clinical management. The need for CT-guided drainage shifts a POPF to Grade C since this is an invasive procedure (Table 1).

#### Secondary endpoints

Secondary endpoints will be postoperative morbidity including wound infection, intra-abdominal collection, delayed gastric emptying [18], postpancreatectomy haemorrhage [19], abdominal rupture, operation time, operative or interventional revisions, in-hospital mortality, duration of intensive care and hospital stay, need for readmission, and quality of life before operation, before discharge and at least 40 days after index operation according to the EQ-5D questionnaire (http://www.euroqol.org) (Table 4). The questionnaire that will be administered 40 days after the operation will be paper-based and sent to patients by post.

**Table 4 T4:** Summary and definitions of secondary outcomes

**Outcome parameter**	**Definition**
**Wound infection**	Surgical site infection associated with laparotomy that develops during the hospital stay
**Intra-abdominal collection**	Fluid collections in the surgical site with or without signs of infection, usually shown in CT-scans
**Delayed gastric emptying (DGE)**	Inability to tolerate solid food with prolonged need for nasogastric tube for at least four days or nasogastric re-intubation after POD 3; grading of DGE depends on its impact on clinical course and management; three grades are used for differentiation [18]
**Postpancreatectomy haemorrhage (PPH)**	PPH is classified, according to time of onset (early vs. late), severity (mild vs. severe) and diagnostic and therapeutic consequences (observation, transfusion, interventional, operative), into three grades [19]
**Abdominal rupture**	Dehiscence of abdominal closure with need for relaparotomy during 40 days after index operation
**Operation time**	Time from skin incision to closure of wound (minutes)
**Operative or interventional revisions**	All actions for diagnostic or therapeutic reasons that are related to an abnormal postoperative course are documented for analyses.
**In-hospital mortality**	Death of any cause during hospital stay
**Need for readmission**	Readmission to any hospital due to postoperative complications
**Quality of life**	Quality of life, accessed by using the EQ-5D questionnaire (EuroQol Group Foundation)

### Methods for avoiding bias

#### Minimizing systemic bias

Block randomisation will be used to ensure that patient groups are comparable. Randomisation will be performed by study nurses attached to the clinical study centre at the Department of Surgery at the University of Heidelberg. The decision of whether to perform a distal pancreatectomy or a pancreaticoduodenectomy cannot be made before abdominal exploration has been performed. Therefore, randomisation will be performed as soon as the decision on a resection strategy has been achieved by the surgeon. However, if patients are excluded after randomisation, e.g., because of a need for total pancreatectomy, the randomisation number will not be reused.

#### Minimizing treatment bias

Although the coverage procedure is a technically simple method and quick to perform, we predict that surgeons who are unfamiliar with it will experience a learning curve until they overcome their individual technical difficulties. At the trial institution, however, the coverage procedure has been performed since 2009, so all surgeons participating in the study are familiar with it.

#### Minimizing measurement bias

Detection and grading of primary and secondary endpoints will be based on records kept during the hospital stay. Members of the study team will not be involved in treatment decisions. Blinding is not needed since occurrence of POPF is an objective endpoint that cannot be influenced by the patient [20]. Blinding of the surgeon is not feasible.

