### Preliminary data

Ever since distal pancreatectomies were first performed, there has been a longstanding debate as to the most effective technique for closure of the pancreatic remnant. For a long time, several different techniques were practiced side-by-side without good evidence in favour of or against any of them [5,6]. In 2005, a systematic review and meta-analysis verified this lack of evidence. Due to compromised comparability because of non-standardised surgical procedures or varying definitions of a POPF, the rates ranged from 0% up to 60% [7]. The DISPACT trial compared the two most commonly used techniques (hand-sewn suturing vs. stapler closure) in a large randomised multicentre trial. In that trial, the detected POPF rate was 36%, demonstrating that secure primary closure of the pancreatic resection margin is far from assured with the current techniques [3].

Recent reports have highlighted the potential advantage of additional coverage of the pancreatic remnant with autologous serous peritoneal tissue [5,6,8-13]. A prospective series from our institution confirmed that reduced rates of POPF were associated with shorter hospital stays and reduced treatment costs [14]. Closure with autologous patches is not a new technique, but it has long been underused. In the 1970s, peritoneal and pleural patches were used to prevent leakages in anastomoses after oesophageal and colorectal resections [15,16]. The falciform patch was initially used in the closure of duodenal and gastric perforations in high-risk patients [16]. In 2006, its use in the context of distal pancreatectomies was first described when skeletonised vessels were wrapped with a falciform patch to protect them from erosion bleeding due to POPF [17]. Iannitti et al. introduced the use of the falciform patch to cover pancreatic anastomoses in order to prevent POPF in pancreaticoduodenectomies and distal pancreatectomies in a retrospective series [10]. However, the results of recent studies highlighting this technique in distal pancreatectomies have to be interpreted with caution due to certain methodological drawbacks including mixed populations, inadequate or missing control groups, and non-uniform definitions of POPF.

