### Sample size calculation

The sample size calculation is based on the expected rate of POPF after distal pancreatectomy with and without additional coverage of the pancreatic remnant. The expected POPF rate of 16% in the experimental group is based on the results of all available studies [5,6,8-10] in which coverage of the remnant was performed and the internationally accepted definition of POPF was used (according to ISGPF [4]; Table 1). The POPF rate in the control group is expected to be 36% based on the 30-day follow-up results of the DISPACT trial in which no group received additional coverage. With alpha = 5% and beta = 20%, a sample size of n = 75 per group is necessary to detect a difference between the two groups when the χ^2^ test (two-sided analysis) is used. It can be expected that including covariates of prognostic importance (age, BMI, and extent of resection) in the logistic regression model that is applied in confirmatory analysis will increase the power as compared to that of the χ^2^ test.

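### The measurement-bias section bases endpoint detection on hospital-stay records, contradicting the planned post-discharge follow-up and the 30-day planning rate; no single window for POPF is fixed

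*Protocol article*

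**What the plan says.** Three parts of the protocol article bear on where endpoint data come from and when collection ends.

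- **Minimizing measurement bias:** "Detection and grading of primary and secondary endpoints will be based on records kept during the hospital stay". The sentence covers primary and secondary endpoints alike.
- **Postoperative data collection:** "The DISPACT trial demonstrated an increased rate of POPF (30% to 36%) between day 7 and day 30", which the article puts down to readmissions. It therefore plans that "DISCOVER patients will be called by phone at least 40 days after the operation to record postoperative development", and says this is to make endpoint assessment accurate. It also plans a review of all medical documents once the patient has left hospital.
- **Sample size calculation:** "The POPF rate in the control group is expected to be 36% based on the 30-day follow-up results of the DISPACT trial"; "The expected POPF rate of 16% in the experimental group is based on the results of all available studies"; "With alpha = 5% and beta = 20%, a sample size of n = 75 per group is necessary", for a two-sided chi-square test.

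The Primary endpoint section defines POPF by drain amylase and names no last day on which onset counts. Table 3 marks endpoint assessment at day 40 and again at an optional three-month visit. It schedules drain enzyme levels only for ward visits and the day of discharge. Table 4 includes abdominal rupture within 40 days and readmission to any hospital.

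**The concern.** For a binary primary endpoint, the observation window decides who counts as an event. One section ends the source data with the hospital stay; another explains why that would miss fistulas. A data manager or endpoint assessor following the first would not count a fistula first recognised at readmission, whereas one following the second would.

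Two things are at stake. First, the control rate behind the sample size comes from 30-day follow-up, so an endpoint closed at discharge would probably show a lower rate and less power than stated. Second, discharge is a decision taken after randomisation in an unblinded trial, so a window ending there need not be the same length in both arms. Leaving the window open also allows it to be settled after outcomes have been seen.

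**Working it through.** **1. The sections side by side**

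| Section | Source or window implied |
|---|---|
| Minimizing measurement bias | Records of the hospital stay |
| Sample size calculation | 30-day rate for controls |
| Adverse events; Table 3 | Telephone contact on day 40 |
| Postoperative data collection | Document review after discharge; call at day 40 or later, no upper limit |
| Secondary endpoints, Table 4 | Rupture to 40 days; readmission to any hospital; quality of life at day 40 or later |
| Table 3, last column | Endpoint assessment at an optional three-month visit |
| Primary endpoint | No window |

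The first row cannot hold literally for the secondary endpoints: readmission cannot be read from the index-stay record. For the primary endpoint it conflicts directly with the reason given for the telephone call.

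**2. Reproducing the stated sample size**

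Inputs, all from Sample size calculation: p1 = 0.36, p2 = 0.16, two-sided alpha 0.05, power 0.80. With p̄ = (p1 + p2)/2 and no continuity correction,

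n = [1.960·√(2p̄(1−p̄)) + 0.842·√(p1(1−p1) + p2(1−p2))]² / (p1 − p2)²

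Here p̄ = 0.26, the first root is 0.6203 and the second 0.6040, so n = 74.3, rounded up to **75 per group**. The stated figure reproduces.

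**3. Power at 75 per group**

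Power = Φ{[(p1 − p2)·√75 − 1.960·√(2p̄(1−p̄))] / √(p1(1−p1) + p2(1−p2))}

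At 36% vs 16%: (0.20 × 8.660 − 1.960 × 0.6203)/0.6040 = 0.855, giving power **80.4%**.

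**4. If only hospital-stay records counted**

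The article gives no length of stay, so the share of fistulas captured in hospital has to be assumed. Its only figure is the DISPACT pair: 30% at day 7 against 36% at day 30, a captured share of 30/36 = 0.833. The same share is applied to both arms.

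| Captured share, both arms (assumed) | Control | Coverage | Power, 75 per group | n per group for 80% |
|---|---|---|---|---|
| 100% (planned follow-up used) | 36.0% | 16.0% | 80.4% | 75 |
| 95% | 34.2% | 15.2% | 77.5% | 80 |
| 90% | 32.4% | 14.4% | 74.5% | 86 |
| 83.3% (day 7 as proxy for the stay) | 30.0% | 13.3% | 70.1% | 95 |

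If patients stay beyond day 7, the captured share lies above the last row and the loss is smaller.

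**The case against.** The strongest reply is that follow-up is already planned. The data-collection section is the operative one. It provides the document review and the call, and Table 3 marks endpoint assessment at day 40. The measurement-bias sentence does not say that hospital records are the only source; it may simply name the main one. Moreover, POPF of any grade is defined by drain amylase, measured on the wards up to discharge, so most events should appear there. A condensed article may also leave an exact cut-off day to the full protocol.

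Much of this stands. The defect is a contradiction, not an absence of follow-up, and the sample size is not wrong. But the sentence states a rule for all endpoints, and the article nowhere says that the other section takes precedence.

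A reader might infer more than the article supports:

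- **That the 36% rests on fistulas arising after discharge.** Only 6 of the 36 points belong to the later period. That period is day 7 to day 30, not shown to lie wholly after discharge.
- **That power would fall to 53%** (30% vs 16%). That lets controls lose late fistulas while the coverage arm loses none, and nothing in the article supports loss in one arm only.
- **That the error favours coverage**, because the institution's own series found that "reduced rates of POPF were associated with shorter hospital stays". That links shorter stay to having fewer fistulas. With equal fistula rates it gives no reason for earlier discharge with coverage. Any figure for inflated type I error would need capture rates by arm, for which the article offers no source.

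**Conclusion.** The point holds as an internal contradiction on the primary endpoint, in a sentence that is wrong as written. Endpoint ascertainment cannot both rest on hospital-stay records and rely on the follow-up that the article plans in order to catch later fistulas.

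Its size is conditional. With the planned follow-up, 75 per group gives 80.4% power and nothing in the calculation changes. With the sentence applied literally, power is about 70% if day 7 stands in for the hospital stay, and about 74–78% at 90–95% capture. Both results assume equal proportional loss in the two arms. Unequal capture by arm is possible with a window that closes at discharge in an unblinded trial, but neither its size nor its direction can be estimated from the article. The missing onset window would matter less alone; here it leaves the contradiction unresolved.

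**What to change.** Amend the measurement-bias sentence to agree with Postoperative data collection, and add one window to the primary endpoint definition:

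- Count POPF with onset up to a single fixed postoperative day for every patient, whenever the call is actually made. Day 40 fits the planned contact.
- Name the sources for detection and grading: inpatient records, the planned post-discharge document review, readmission records and the day-40 call.
- Do not count onset after that day, including anything found at the optional three-month visit.
- Report a day-30 cut-off as a sensitivity analysis, because the 36% is a 30-day rate.

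The change is one of wording, since the contact and the document review are already planned. As recruitment was still under way when the article appeared, it should be made before outcomes are reviewed. There is one small cost: drain enzymes are scheduled only up to discharge, so later fistulas must be classified from whatever outpatient and readmission records exist. No new measurements are required, and the report should state this limit.

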### Statistical methods

#### Analysis

Each patient’s allocation to one of the two analysis populations will be defined prior to the analysis and will be documented in the statistical analysis plan. We will distinguish between the following subpopulations: all patients who were randomly assigned to one of the groups will be analysed in the full analysis set according to the intention-to-treat principle. The per protocol analysis set will include patients without major protocol deviations, while in the safety analysis set patients will be analysed according to treatment rather than randomly. During data review, deviations from the protocol will be assessed as “minor” or “major”. Major deviations from the protocol will lead to the exclusion of the patient from the per protocol analysis set.

#### Confirmatory analysis

The null hypothesis of the proposed trial assumes that the rate of POPF type A–C is equal in the two intervention groups. A binary logistic regression model will be applied in order to compare POPF-rates in the two groups, adjusting for age, BMI and extent of resection. Confirmatory analysis will be based primarily on the full analysis set, which is consistent with the intention-to-treat principle as it includes all patients as randomised. Missing values will be replaced by means of the ICA-r method described by Higgins et al. [18]. Additionally, sensitivity analyses will be performed according to alternative methods for dealing with missing data, such as complete case analysis. In the final analysis, c_alpha = 0.0087 (alpha = 0.05, two-sided) will be applied.

Concerning the secondary endpoints, exploratory data analysis will be performed calculating appropriate summary measures for the empirical distribution (mean, standard deviation, median, minimum and maximum for continuous variables, and frequencies and percentages for categorical variables) as well as descriptive two-sided *P* values. Sensitivity analyses will be conducted for the perprotocol population as well as for the appropriate subgroup (e.g., covering methods). The safety analysis will include calculation and comparison of frequencies and rates of complications and SAEs. Furthermore, statistical methods will be used to assess the quality of the data and the homogeneity of the intervention groups. All analyses will be performed using SAS version 9.1 or higher.

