**Methods/Design:**

DISCOVER will aim to investigate differences in the postoperative course after a distal pancreatectomy comparing the standard surgical technique with an alternative technique that provides additional coverage of the pancreatic remnant by the falciform ligament. The primary endpoint of this trial will be the rate of POPF. As secondary endpoints, incidence of postoperative morbidity and mortality, length of hospital stay, and quality of life will be assessed.

DISCOVER is a single-centre, randomised, controlled surgical trial. For statistical analysis, a binary logistic regression model will be used. With a level of significance of 5% and a power of 80%, a sample size of 75 patients per group has been identified as necessary.

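### The final analysis is given a critical value of 0.0087, which belongs to a product of two stage-wise p-values, but the article describes a one-stage trial with one test

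*Protocol article*

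**What the plan says.** The Sample size calculation section sets out a fixed design. Its inputs are "The POPF rate in the control group is expected to be 36"% and "The expected POPF rate of 16% in the experimental group". It concludes: "With alpha = 5% and beta = 20%, a sample size of n = 75 per group is necessary", on the basis that the chi-square "test (two-sided analysis) is used". The Methods/Design part of the abstract repeats this: "With a level of significance of 5% and a power of 80%, a sample size of 75 patients per group".

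The Confirmatory analysis section names one test: "A binary logistic regression model will be applied in order to compare POPF-rates in the two groups, adjusting for age, BMI and extent of resection". After its sentences on missing data it adds: "In the final analysis, c_alpha = 0.0087 (alpha = 0.05, two-sided) will be applied".

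The symbol c_alpha is not defined, and no statistic is named for comparison with it. Nowhere does the article mention an interim analysis, a first stage, a first-stage p-value, stopping bounds, a combination test or sample size re-estimation.

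**The concern.** This sentence decides whether the trial is positive on its primary endpoint. The design described yields one p-value, from one logistic regression, in a trial sized at 5%. A critical value of 0.0087 has no place in that design. It does have a place in a two-stage design that multiplies two p-values, but no such design is described.

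Two thresholds, 0.05 and 0.0087, can therefore be read from one sentence. At the planned sample size they disagree over a plausible range of results. An analyst who took 0.0087 as the cut-off for the single p-value would apply a far stricter test than the one the trial was sized for.

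**Working it through.** **Inputs.** Control rate 0.36, coverage rate 0.16, two-sided alpha 0.05, power 0.80 and 75 per group come from Sample size calculation. The critical value 0.0087 comes from Confirmatory analysis.

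**1. Reproduce the stated sample size.** The mean rate is (0.36 + 0.16)/2 = 0.26. Use the pooled-variance formula without continuity correction:

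n = [1.960·√(2·0.26·0.74) + 0.842·√(0.36·0.64 + 0.16·0.84)]² / 0.20²

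The two square roots are 0.6203 and 0.6040, so n = 74.3, rounded up to **75**. The stated figure reproduces exactly as a one-stage two-sided 5% calculation.

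**2. Identify 0.0087.** Under the null hypothesis, −2·ln(p₁·p₂) for two independent p-values follows a chi-square distribution with 4 degrees of freedom. Its 95% point is 9.488, so the critical value for the product is exp(−9.488/2) = 0.008705, or **0.0087**. As a check, P(p₁·p₂ ≤ c) = c·(1 − ln c), and at c = 0.0087 this is 0.0500. The number and the bracketed alpha of 0.05 therefore agree with each other, but only for a product of two p-values.

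**3. Power if 0.0087 is instead applied to the single final p-value.** Power = Φ{[0.20·√75 − z·0.6203]/0.6040}.

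| Two-sided cut-off | z | Argument of Φ | Power (normal approximation) | Power (exact enumeration) |
|---|---|---|---|---|
| 0.05 | 1.960 | 0.855 | 80.4% | 80.8% |
| 0.0087 | 2.624 | 0.173 | 56.9% | 58.1% |

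Holding 80% power at 0.0087 would need 115 per group (step 1 with z = 2.624 gives 114.04).

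**4. Where the two readings disagree.** Take 27/75 control events (36%) and the unadjusted chi-square test.

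| Coverage-arm events | p | At 0.05 | At 0.0087 |
|---|---|---|---|
| 12/75 | 0.0052 | positive | positive |
| 13/75 | 0.0097 | positive | negative |
| 16/75 | 0.047 | positive | negative |
| 17/75 | 0.073 | negative | negative |

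Results of 13 to 16 events are positive on one reading and negative on the other. The planning assumption itself, 16% of 75 = 12 events, only just passes the stricter cut-off.

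Steps 3 and 4 use the unadjusted test. The confirmatory model adjusts for three covariates, and the article expects that this "will increase the power as compared to that of the" chi-square test. It gives no figure for the gain.

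**The case against.** The strongest defence is that 0.0087 is not offered as a significance level. The sentence writes c_alpha, not alpha, and gives alpha = 0.05, two-sided, in the same breath. It never says that the logistic-regression p-value is compared with 0.0087. The value is numerically right for a two-stage product test at 5%, and no arithmetic in the article is in error. On this view the sentence is either a condensed reference to a two-stage plan or text left over from one. An article may leave stage timing and stopping bounds to the full protocol or the analysis plan.

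Much of this stands. A reader might infer that the trial will be run at 0.87% with 57% power. The article does not support that as fact, because the stated alpha contradicts it; it is the result of one literal reading. A reader might also infer that the rule is fixed nowhere and the threshold could be picked after the data are seen. That depends on documents not shown. Nor do the documents support criticism of how a two-stage product test would behave here, since they contain no stages, no split and no combination rule to criticise.

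What does not stand is the appeal to condensation. The complaint is not that interim details are absent. The article prints a specific critical value for its primary test, and that value does not fit the one-stage sizing and single test it also prints. That is a contradiction within the text.

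**Conclusion.** The point holds as an internal contradiction in the confirmatory decision rule. The critical value belongs to a product of two p-values at overall alpha 0.05, while the article describes one stage, one test and a one-stage 5% sample size that reproduces at 75 per group. The sample size itself is not in question.

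The consequence is conditional. If 0.0087 were applied to the single final p-value, the type I error would be 0.87% instead of 5%, and power would be about 57% (exact 58%) instead of 80%. This assumes 36% versus 16%, 75 per group and the unadjusted chi-square test; the adjusted model may do somewhat better, by an amount the article does not give. If a two-stage product rule is in force, overall alpha stays at 5% and the 57% does not apply. The article cannot show which is the case. Because the sentence governs the primary conclusion, it needs to be settled.

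**What to change.** Settle the sentence before database lock, in one of two ways.

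- **If the trial is single-stage, as described:** replace the sentence with *The treatment coefficient in the adjusted logistic regression is tested at two-sided alpha = 0.05.* This matches the sample size calculation.
- **If a two-stage design is in force:** say that 0.0087 bounds the product of the stage-wise p-values and not the final p-value. Give the timing of stage 1, any stopping bounds and the sidedness of the stage p-values. Restate the power for that rule, since the 80% now quoted is for a one-stage test.

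The first option costs one sentence. The second costs a short paragraph and a power calculation. Correcting the text in itself adds no patients. The Trial status section says recruitment was still open, so on the article's own account this could be done before the final data are seen.
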